### Sample Size

We computed power to detect differences between the intervention arms in a crossover trial via analysis of variance with level of significance set to 0.05 (SAS software v9.3). We assumed baseline levels and patterns of change similar to those reported in King 2013 [28]. We examined the significance of treatment effect from 1000 simulated replications of a crossover trial. The trial is comfortably powered (85 %) with 120 patients if total Mini-BESTest score increases by 2.4 points on average in the ABC arm, and only 1.3 points on average in the control arm. We predict a roughly 20 % drop-out rate, which is conservative based on our previous experience with short duration trials of rehabilitation in PD and by others [24, 25, 28, 29].

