### Primary outcome measure – Mini-BESTest

The primary outcome measure on which the intervention study was powered is the clinical *Mini-BESTest.* [35] The *Mini-BESTest* [35] is a sensitive measure of dynamic balance and includes 14 items (a maximum and best score of 28) [36, 37].

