#### Statistical Analysis

First, we will compare the amount of improvement in the Mini-BESTest with an analysis of covariance (ANCOVA) model, controlling for age. It is possible that lower functioning patients will have larger adaptation to ABC-C since they start out with less function. Alternatively, it is possible that the lower functioning patients will have poorer exercise tolerance so will improve less so we will also control for baseline Mini-BESTest*.* Because we are utilizing a crossover design, the treatment effect will represent change during the ABC-C versus control rehabilitation periods regardless of whether a patient received the ABC-C intervention during period 1 or period 2. We will assess, but do not anticipate, period by treatment group interaction effects. We will also enter an interaction term into the model to assess for differential intervention effects cognitive and/or frontal lobe structural and functional connectivity status. Second, we will relate the percent improvement in the Mini-BESTest with ABC-C intervention with baseline measures of posture/gait impairments, cognitive impairments and both structural and functional connectivity of the Posture/Locomotor circuit at baseline with linear regression models. Previous studies have shown the Minimal Detectable Change of the Mini-BESTest was 3 points [52]. We will also determine how many subjects move from high- to low-fall risk; a cutoff score for identifying PD fallers from non-fallers with the Mini-BESTest is 19/28 (63 %), with a sensitivity of .98 in 80 subjects [53].

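### The fall-risk cutoff is given as 19/28 and as 63 %, which are different thresholds on the 28-point Mini-BESTest (minor)

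*Protocol article*

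**What the plan says.** All of this is in the protocol article.

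- **Threshold (Statistical Analysis):** "a cutoff score for identifying PD fallers from non-fallers with the Mini-BESTest is 19/28 (63", followed by the per cent sign that closes the bracket.
- **Accuracy quoted for it (same sentence):** "with a sensitivity of .98 in 80 subjects". No specificity is given.
- **Use of the threshold (same sentence):** "We will also determine how many subjects move from high- to low-fall risk".
- **Scale (Primary outcome measure – Mini-BESTest):** the test "includes 14 items (a maximum and best score of 28" points. Higher is better, so high fall risk lies at the low end.
- **Measurement error (Statistical Analysis):** the "Minimal Detectable Change of the Mini-BESTest was 3 points".

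The article does not say whether a patient scoring exactly at the cutoff is high or low risk.

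**The concern.** A cutoff written both as a score and as a percentage should give the same classification either way. Here it does not, and the number is not mere background: it is the rule that sorts patients into high and low fall risk for an analysis the article says it will carry out. Whoever programs that analysis from the text can take either figure, and the two put some patients in opposite classes. That changes who can be counted as having moved and who has moved.

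If the choice between the two is left until scores are in hand, it becomes a choice made after seeing the data. If the error lies in the score rather than the percentage, the quoted sensitivity might not apply to the rule that is used.

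**Working it through.** **Inputs.** Cutoff 19/28 and 63 % (Statistical Analysis); maximum score 28 (Primary outcome measure – Mini-BESTest); 120 patients and an assumed mean gain of 2.4 points with exercise (Sample Size).

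**1. Reproduce the stated percentage.** 100 × 19 / 28 = 67.9 %. The article states 63 %, so its figure is not reproduced. The gap is 67.9 − 63 = 4.9 percentage points.

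**2. Work back from the percentage.** 0.63 × 28 = 17.64 points, which is 19 − 17.64 = 1.36 points below the raw cutoff.

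**3. Could rounding explain it?** To round to 63 %, a score would have to lie between 0.625 × 28 = 17.50 and 0.635 × 28 = 17.78. No whole number does. The neighbours are 17/28 = 60.7 % and 18/28 = 64.3 %.

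**4. Could another denominator explain it?** 19/30 = 63.3 % and 20/32 = 62.5 % would both fit. The article gives no scale other than 28 points, so this shows only that a differently scored version is arithmetically possible.

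**5. Classify the scores near the cutoff.**

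| Score | Share of 28 | Raw rule, 19 or less is high | Raw rule, below 19 is high | 63 % rule (17.64 or less is high) |
|---|---|---|---|---|
| 17 | 60.7 % | high | high | high |
| 18 | 64.3 % | high | high | low |
| 19 | 67.9 % | high | low | low |
| 20 | 71.4 % | low | low | low |

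A score of 18 conflicts under either boundary convention. A score of 19 conflicts only if 19 itself counts as high risk.

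**6. Illustrative size.** The article gives no baseline mean or SD, so what follows is assumption. Baseline is normal, rounded to whole scores and limited to 0–28; the change has mean 2.4 and an assumed SD of 2.5; there are 120 patients and no drop-out. The last three columns give the simulated number moving from high to low risk when high risk is 19 or less, 18 or less, and 17 or less.

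| Baseline mean | SD | Patients scoring 18–19 | 19 or less | 18 or less | 17 or less |
|---|---|---|---|---|---|
| 17 | 3 | 27.8 | 36.3 | 36.5 | 33.3 |
| 17 | 4.5 | 20.0 | 26.2 | 26.1 | 24.9 |
| 17 | 6 | 15.4 | 19.9 | 19.9 | 19.4 |
| 19 | 3 | 30.9 | 33.3 | 28.0 | 21.2 |
| 19 | 4.5 | 21.0 | 24.9 | 22.6 | 19.8 |
| 19 | 6 | 15.8 | 19.4 | 18.3 | 16.9 |
| 21 | 3 | 22.4 | 21.3 | 14.7 | 9.3 |
| 21 | 4.5 | 18.1 | 19.6 | 16.4 | 13.0 |
| 21 | 6 | 14.6 | 17.1 | 15.2 | 13.2 |

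Between 19-or-less and 17-or-less, the count differs by 0.5 (19.9 − 19.4) to about 12 (33.3 − 21.2). Between 18-or-less and 17-or-less, it differs by 0.5 to 6.8 (28.0 − 21.2).

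**The case against.** The best defence is that the raw figure governs. The Mini-BESTest is scored in points, the article gives a cutoff in points on its own 28-point scale, and 63 % corresponds to no attainable score. On that reading the percentage is a slip in a bracket, 18 is plainly high risk, and the only open matter is which side 19 falls on. This is a good argument and probably the more natural reading. It does not close the matter: the source of the cutoff is not at hand, and 63 % fits other denominators, so the documents alone cannot rule out that the score is the figure at fault.

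Three stronger readings are tempting and should not be drawn.

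- **That patients scoring 18 or 19 have no risk class.** They do have one. Taken literally, the two figures give a score of 18, and possibly 19, conflicting classes.
- **That a main result of the trial is compromised.** The primary analysis is the ANCOVA of Mini-BESTest improvement. The cutoff does not enter that model, the sample size, eligibility or the planned regressions. Fall-risk class is not listed in Table 2, and the count has no stated test.
- **That the count will be made without an education comparison.** The sentence is silent on this. The same section defines the treatment effect as change in the ABC-C versus control periods, and the layout of a descriptive table is commonly left to an analysis plan, which is not shown here.

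It is also fair to say that chance crossings occur with any cutoff, so they are not a consequence of this error.

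**Conclusion.** The statement is wrong as written, and the severity is minor. That 19/28 is 67.9 %, that 63 % of 28 is 17.64, and that no whole score out of 28 gives 63 % follow from the article's own numbers without any assumption. So does the opposite classification of a score of 18. The conflict at 19 depends on a boundary convention that the article does not state. Which of the two figures is mistaken cannot be settled from the documents.

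The practical size rests wholly on the assumed baselines: about 15 to 31 of 120 patients at 18 or 19, and a shift in the high-to-low count of anything from under one patient to about 12. The shift arises only if the percentage is applied in place of the raw score.

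**What to change.** Before any patient is classified:

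1. Check the raw score and the percentage against the cited source, including which scoring version of the test it used.
2. State one whole-number rule on the 28-point scale, saying whether the boundary score is high or low risk, and correct or delete the other figure.
3. Confirm that the quoted sensitivity belongs to that rule and that scoring version.

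Optionally, tabulate moves in both directions, high to low and low to high, for the ABC-C and the education periods. A one-point crossing of the cutoff lies within the 3-point Minimal Detectable Change that the article quotes, so a count in one direction is hard to interpret alone.

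The cost is one source check and one corrected sentence, plus a small table if the option is taken. The sample size and the primary analysis stay as they are.

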## Discussion

The overarching goal of this study is to determine if cognitive function and frontal brain circuitry deficits predict responsiveness to exercise. Specifically, we are interested in understanding if certain phenotypes that best predict responsiveness to high intensity, short duration agility rehabilitation with a focus on cognition will help guide therapists to identify candidates for therapy and to develop specific therapy for specific types of mobility disabilities from parkinsonism. To date, there are very few studies on cognitive contributions to gait and balance as they relate to rehabilitation, particularly in this challenging population. Currently, physical therapists do not routinely incorporate cognitive challenges for people with PD and furthermore, it is unclear if these patients will benefit from such training.

If we find that executive function deficits and reduced structural and/or functional connectivity of the locomotor circuitry predict poor responses to challenging balance rehabilitation, that supports our hypothesis that frontal (and prefrontal) lobe impairments limits rehabilitation efficacy. If particular impairments of balance and gait improve more than others with ABC-C, this information will be used to improve the ABC-C intervention and will be followed by studies focused on determining which postural domains are most amenable to improvement with rehabilitation. The results from this study will further our understanding of the relationship between cognition and mobility with a focus on brain circuitry as it relates to rehabilitation potential.

## Abbreviations

ABC: Agility boot camp
ABC-C: Agility boot camp-cognition
ABC: Activities-specific balance confidence scale
ANCOVA: Analysis of covariance
DTI: Diffusion tensor imaging
ED: Education
EX: Exercise
MoCA: Montreal cognitive assessment
MDS UPDRS: Movement disorders society unified Parkinson’s disease rating scale
PD: Parkinson disease
PDQ-39: Parkinson disease questionnaire-39
REDCAP: Research electronic data capture
*rs*-*f*MRI: Resting-state functional MRI
SCOPA-COG: Scales for outcome of Parkinson’s disease-cognition
